### Sample size

2.3

The calculation of the sample size is based on the visual analog scale (VAS)score results 1 month after the operation. According to the pre-test results, the average score of the experimental group is estimated to be 3.4 points and the standard deviation is 1.8. The control group averaged 4.6 and the standard deviation is 1.9. This study is a non-inverse design, 1-sided test, α =0.025, power = 90%, through calculation, each group needs 50 patients in total, and the estimated withdrawal rate is 20%. Each group will include 63 patients.

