### Postoperative rehabilitation and follow-up

2.8

All patients undergo rehabilitation training according to the standard plan. Postoperatively, the shoulder joint fixation device is used to fix the affected shoulder at 30° internal rotation and 20° abduction. From 0 to 6 weeks after surgery, mainly passive activities, the main actions: pendulum, forward bend, lift and external rotation, forward flexion and abduction should not exceed 90°; active exercise will be started after 6 weeks; physical labor is allowed after 6 months or sports. After 3, 6, and 12 months outpatient follow-up, X-ray and MRI examination of the shoulder joint are performed.

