#### Data collection and management

2.8.1

During each follow-up, 1 to 2 assistants will collect the follow-up data according to the evaluation criteria, and record them clearly in a pre-designed form combined with the basic information of patients. The information and data of all patients will be collected and stored in a fixed storage room to protect the confidentiality before, during and after the trial. Access to the database is limited to the researchers of this research group.

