#### Statistical analysis

2.8.2

We will use SPSS 16.0 statistical software for statistical analysis. Continuous variables were described as the mean ± standard deviation, and differences between groups were analyzed using a series of 1-way analysis of variance (ANOVA) with Bonferroni post-hoc test, while differences between groups over time were analyzed using multi-way ANOVA with Bonferroni post-hoc test. Categorical variables were described as the number (%), and were analyzed by Fisher exact test. A *P* value of < .05 was considered statistically significant.

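### The over-time comparison is a multi-way ANOVA with no within-patient term; taken as written, its time-averaged group test is too liberal and its group-by-time test too conservative

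*Protocol article*

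**What the plan says.** Section 2.8.2 (Statistical analysis) of the protocol article divides the analysis of continuous outcomes in two. For group comparisons without reference to time, "differences between groups were analyzed using a series of 1-way analysis of variance (ANOVA) with Bonferroni post-hoc test". For the course over time, "differences between groups over time were analyzed using multi-way ANOVA with Bonferroni post-hoc test". A P "value of < .05 was considered statistically significant".

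The data are repeated on the same patients. Section 2.8 states: "After 3, 6, and 12 months outpatient follow-up, X-ray and MRI examination of the shoulder joint are performed". Section 2.8.1 adds: "During each follow-up, 1 to 2 assistants will collect the follow-up data according to the evaluation criteria". Section 2.3 uses one more time point, since the sample size is "based on the visual analog scale (VAS)score results 1 month after the operation". Read together, these give three visits with scores per patient, or four if the 1-month VAS is counted.

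The article mentions no repeated-measures or mixed model, patient term, within-subject factor or sphericity correction.

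**The concern.** An ordinary group-by-time ANOVA treats each score as a separate, independent observation and tests every effect against one residual. Pain and function scores from the same shoulder a few months apart can be expected to correlate positively. The pooled residual then mixes variation between patients with variation within patients and is the wrong yardstick for two effects:

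- The group effect averaged over visits should be judged against variation between patients. The pooled residual is too small for this, so P values are too small.
- The group-by-time effect should be judged against variation within patients. The pooled residual is too large for this, so P values are too large.

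The second effect matters for this trial's rationale. The Introduction wants tendon healing that is quicker as well as stronger, and a faster recovery appears as a group-by-time difference. The Bonferroni step does not help, because it adjusts for the number of comparisons and leaves the error term as it is.

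**Working it through.** **1. The plan's own figure.** Inputs from section 2.3: means 3.4 and 4.6 (difference 1.2), SDs 1.8 and 1.9, one-sided alpha 0.025, power 90%.

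n per group = (1.8² + 1.9²) × (1.960 + 1.2816)² / 1.2² = 6.85 × 10.507 / 1.44 = 49.98, so 50. With 20% withdrawal, 50 / 0.8 = 62.5, so 63. Both figures reproduce, and this point does not touch them.

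**2. What the pooled error does.** Let k be the number of visits, σ² the variance of a score and ρ the correlation between two scores from one patient, taken as equal for all pairs. The pooled residual estimates σ².

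- An arm mean over k visits has variance σ²[1 + (k−1)ρ]/(nk), whereas the model assumes σ²/(nk). The group F is inflated by 1 + (k−1)ρ. Actual type I error ≈ 2 × [1 − Φ(1.96 / √(1 + (k−1)ρ))].
- A group-by-time contrast has variance proportional to σ²(1−ρ), whereas the model assumes σ². The interaction F shrinks by (1−ρ). Actual type I error ≈ P(χ² on k−1 df > c/(1−ρ)), where c = 5.99 for k = 3 and 7.81 for k = 4.

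Worked case, k = 3 and ρ = 0.5:
- Group: 2 × [1 − Φ(1.96/√2)] = 16.6%.
- Group-by-time: exp(−5.99/(2 × 0.5)) = exp(−5.99) = 0.25%.

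**3. Range.** The documents give no ρ, so 0.3 to 0.7 is assumed. The simulation uses 10,000 trials per setting, 50 per arm and no true effect.

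| Visits | ρ | Group: formula | Group: simulated | Group-by-time: formula | Group-by-time: simulated |
|---|---|---|---|---|---|
| 3 | 0.3 | 12.1% | 11.3% | 1.4% | 1.4% |
| 3 | 0.5 | 16.6% | 16.2% | 0.25% | 0.2% |
| 3 | 0.7 | 20.6% | 21.2% | 0.005% | 0.01% |
| 4 | 0.3 | 15.5% | 15.5% | 1.1% | 1.0% |
| 4 | 0.5 | 21.5% | 21.4% | 0.14% | 0.2% |
| 4 | 0.7 | 26.6% | 26.2% | 0.001% | 0.02% |

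At ρ = 0 all tests are near 5%. With 63 per arm the results agree within simulation error. Repeated-measures ANOVA on the same data held both tests at 4.5% to 5.2%.

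**4. Another correlation pattern.** With correlation that decays over visits (first-order autoregressive, 0.5 to 0.9, 3 or 4 visits, 50 per arm), the group test rejected in 15% to 30% of null trials and the group-by-time test in 1.3% down to 0%. The directions are the same.

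**5. Lost power, for illustration.** Assume an arm difference of 1.2 at the first of three visits that fades linearly to 0 at the third, SD 1.85, 50 per arm. Group-by-time power with ordinary ANOVA against repeated-measures ANOVA was 49% against 68% at ρ = 0.3, 47% against 83% at ρ = 0.5, and 42% against 97% at ρ = 0.7. The fading pattern is an assumption, not a figure from the article.

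**6. What is not affected.** A comparison of the arms at one visit uses one value per patient and has no dependence problem. Even inside the multi-way model, an arm contrast at a single visit has variance 2σ²/n, and the pooled residual estimates σ² correctly if variances are equal across visits. Simulated type I error for such contrasts was 5.1%, 5.4% and 4.7% (3 visits, ρ = 0.3, 0.5, 0.7) and 5.1% (4 visits, ρ = 0.5).

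**The case against.** The strongest reply is that multi-way ANOVA is loose wording, in a condensed article, for a two-way repeated-measures ANOVA, and that the error structure is detail for a fuller document. That is possible, and the article does not say outright that scores are treated as independent. But it does name a method, and nothing around that name points to a within-patient factor. An analyst following section 2.8.2 literally would fit the wrong model. If repeated measures were intended, one sentence settles it.

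A second reply concerns reach, and it stands. Section 2.8.2 sends plain group differences to 1-way ANOVAs. Run visit by visit, these are valid, and so is the 1-month VAS comparison that sizes the trial. A reader might infer that every between-group P value, or the trial's sizing comparison, is invalid. The article does not support that: only the time-averaged group effect and the group-by-time effect from the multi-way model are distorted. If the multi-way model is used for group-by-time alone, the harm is lost power and not false positives.

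A reader might also count the absence of pre-operative scores from the model as an error. It is not. Randomisation makes the unadjusted comparison valid, and adjustment only buys precision.

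**Conclusion.** The point holds for the method as named. It rests on three things: a literal reading of section 2.8.2, positive within-patient correlation (the sizes need an assumed value, the directions do not), and three or four scored visits. In the middle case of three visits and correlation 0.5, the time-averaged group test runs at roughly three times its nominal level. Split evenly by direction, that is about 8.3% of null trials favouring the scaffold (half of 16.6%), against the one-sided 2.5% used for the sample size. The group-by-time test in the same case almost never rejects under the null, and power falls accordingly. The power figures are illustrations only, because they also depend on an assumed pattern of effect. The sample size and single-visit comparisons stand.

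**What to change.** In section 2.8.2, replace the multi-way ANOVA with a linear mixed model for repeated measures: arm, visit and arm-by-visit as fixed effects, with an unstructured within-patient covariance. Report the arm difference with a 95% confidence interval at each visit.

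The minimum alternative is a repeated-measures ANOVA that names visit as the within-patient factor and applies a sphericity correction. The correction is needed: without it, the group-by-time test was mildly liberal under decaying correlation (about 5% to 9%).

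It would also help to state that the 1-way ANOVAs are run at single visits, since that is what keeps them valid.

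Optionally, if pre-operative scores are recorded, add them as a covariate for precision.

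The cost is analysis wording only. Sample size, visits and conduct do not change. The optional covariate requires pre-operative scores on the data form.

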### Evaluation Criteria and Efficacy Judgment

2.7

(1)VAS:^[12]^VAS is often used to measure pain intensity.^[13]^ The patient will be asked to mark a point between 0 and 100, where 100 means maximum pain (far right) and 0 means no pain (far left);(2)American Shoulder & Elbow Surgeons score.^[14]^ The American Shoulder & Elbow Surgeons score includes pain (50 points) and life function (50 points). The full score is 100 points. The higher the score, the better the shoulder joint function;(3)University of California Los Angeles score:^[15]^ Including pain, function, muscle strength and range of motion of the shoulder joint. The total score is 35 points, the higher the score, the better the shoulder joint function;(4)Constant-Murley score:^[16]^ It is the shoulder joint scoring method uniformly adopted by the European Society of Shoulder and Elbow Surgery. It consists of 4 subscales: pain (15 points), muscle strength (25 points), functional activity (20 points) and shoulder joint mobility (40 points). The total score is 100 points, the higher the score, the better the shoulder joint function.(5)X-ray evaluation of postoperative shoulder joint anatomy, MRI evaluation of tendon anchor loosening and displacement and rotator cuff healing.(6)Incision healing grade, incidence of adverse reactions (such as incision infection, anchor loosening, rotator cuff tearing, etc).

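### For uncommon adverse reactions, counts with a Fisher P value at .05 have low power and do not show how much added harm remains possible; a risk difference with a 95% interval would

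*Protocol article*

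**What the plan says.** Item 6 of section 2.7 (Evaluation Criteria and Efficacy Judgment) lists the "incidence of adverse reactions (such as incision infection, anchor loosening, rotator cuff tearing, etc") among the outcomes.

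Section 2.8.2 (Statistical analysis) gives one rule for every categorical outcome: "Categorical variables were described as the number (%), and were analyzed by Fisher exact test". A P "value of < .05 was considered statistically significant". No separate rule for safety is stated, so this one covers adverse reactions. The section does not say whether the test is one- or two-sided.

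Section 2.3 (Sample size) rests on VAS pain 1 month after surgery: "each group needs 50 patients in total, and the estimated withdrawal rate is 20" per cent, then "Each group will include 63 patients". No adverse event enters that calculation.

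**The concern.** The experimental arm receives an implant that releases three growth factors and, according to the introduction and discussion, carries stem cells. The control arm has the repair alone. A reader will therefore ask of the safety data how much extra local harm the implant might cause. A count per arm and a P value do not answer that. When events are few, P will often exceed .05 even if the true rate has risen several-fold, and the output then contains no limit on the size of the harm. At stake is whether the report can state the range of added risk that the trial has and has not excluded.

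**Working it through.** **Inputs from the article.** 63 enrolled and 50 evaluable per arm (section 2.3), 1:1 allocation (section 2.5), Fisher exact test at .05 (section 2.8.2).

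**Assumptions.** The Fisher test is taken as two-sided, since sidedness is not stated. The article gives no adverse event rates, so the true rates below are assumed and shown as a range.

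**Step 1: the plan's own figure.** Section 2.3 assumes VAS means of 3.4 (SD 1.8) with the implant and 4.6 (SD 1.9) without it. With "1-sided test, α =0.025, power = 90" per cent:

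n = (1.8² + 1.9²) × (1.960 + 1.282)² / (4.6 − 3.4)² = 6.85 × 10.51 / 1.44 = 50 per arm, and 50 / (1 − 0.20) = 62.5, rounded up to 63.

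Both stated figures reproduce. The trial has 90% power for the pain difference; nothing is stated for safety.

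**Step 2: where the threshold falls.** For k events against 0 with n per arm, the two-sided Fisher P is 2 × C(n, k) / C(2n, k). For 5 v 0 of 63: 2 × 7,028,847 / 244,222,650 = .0576.

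| Events | P, 63 per arm | P, 50 per arm |
|---|---|---|
| 4 v 0 | .119 | .117 |
| 5 v 0 | .058 | .056 |
| 6 v 0 | .028 | .027 |
| 7 v 1 | .062 | .059 |
| 8 v 1 | .033 | .031 |

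The rule therefore needs 6 events against 0 (9.5% v 0% of 63), or 8 against 1.

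**Step 3: power.** Exact power is the sum, over all pairs (a, b) with two-sided Fisher P < .05, of Bin(a; n, p_E) × Bin(b; n, p_C).

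| Assumed true rates, control v experimental | 63 per arm | 50 per arm |
|---|---|---|
| 1% v 6% | 10% | 5% |
| 2% v 8% | 16% | 9% |
| 2% v 10% | 30% | 19% |
| 5% v 15% | 35% | 24% |
| 2% v 20% | 90% | 78% |
| 5% v 25% | 87% | 75% |

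In the first four rows, a three- to six-fold rise in an uncommon event is missed in about 65% to 95% of trials (100% − 35% and 100% − 5%). The last two rows show that large differences are usually found.

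**Step 4: what an interval adds.** Newcombe's interval combines the Wilson limits of the two arms. For 5/63 (7.9%; Wilson 3.4% to 17.3%) and 0/63 (Wilson 0% to 5.7%):

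- lower limit: 7.9 − √[(7.9 − 3.4)² + (5.7 − 0)²] = +0.6 points
- upper limit: 7.9 + √[(17.3 − 7.9)² + (0 − 0)²] = +17.3 points

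For 4 v 0 of 63 the interval is −0.6 to +15.2 points. With no events among 63 implanted patients, the one-sided 95% upper limit for the event rate is 1 − 0.05^(1/63) = 4.6%. A Fisher P value supplies none of these limits.

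At 5 v 0 the Newcombe interval excludes zero while Fisher gives .058, so the two can disagree near the threshold. The interval methods can also differ from each other: for 4 v 0 of 63, the Miettinen-Nurminen lower limit is +0.4 points against −0.6 for Newcombe.

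**The case against.** The strongest reply has five parts.

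- **Counts and percentages are planned.** A 5 v 0 split would be visible, and a reader could derive the interval. This stands: adverse reactions are not judged by the P value alone. The split would still be labelled non-significant, with no measure of its uncertainty.
- **The rule is not blind.** A reader might infer that the safety comparison will show no difference whatever the truth. The figures do not support that: 6 v 0 is significant, and power is 75% to 90% for 2% v 20% or 5% v 25%. Rotator cuff tearing is among the listed reactions, and the discussion describes the incidence of re-tear as still high, so it is not a rare event. The point is confined to uncommon events.
- **Nothing equates non-significance with safety.** A reader might infer that the plan will report P >= .05 as equal safety. No section says so; section 2.8.2 only defines what is called significant. The misreading is foreseeable, but it is not a stated rule.
- **Sidedness is open.** Read one-sided at .05, 5 v 0 of 63 would be significant (P = .029). At the one-sided .025 of section 2.3 it would not.
- **Interval methods and safety tables are often left to the SAP, Fisher is valid for sparse data, and the low power comes from the sample size.** All of this is fair. Fisher is not an error, and an interval adds no patients. But section 2.8.2 does state the analysis for categorical outcomes, and the proposal changes that stated output to one that shows how imprecise the comparison is.

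**Conclusion.** The point holds in limited form, as a cheap improvement and not as an error that invalidates the plan. In a trial sized on 1-month pain, counts with a Fisher P at .05 have low power for uncommon adverse reactions: about 10% (1% v 6%) and 30% (2% v 10%) with 63 per arm, 5% and 19% with 50. They also give no bound on the added harm. Large differences can be detected, and common events such as re-tear lie outside the rare-event argument. These figures rest on assumed event rates and a two-sided test.

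**What to change.** In section 2.8.2, add two or three sentences:

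- For each type of adverse reaction, report n/N per arm and the risk difference with a 95% confidence interval, by Newcombe or Miettinen-Nurminen, with one method named in advance.
- Base the safety statement on that interval and quote its upper limit for added harm.
- State that P >= .05 is not evidence of equal safety, and that any Fisher P for adverse reactions is descriptive only, because it can disagree with the interval near the threshold.

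The cost is this text and one extra table, with no additional patients or data. The downside is a safety statement less favourable than a report of no significant difference.

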## Discussion

3

At present, the incidence of rotator cuff nonhealing and re-tearing after rotator cuff injury is still high.^[17]^ Most scholars believe that poor healing of the tendon at the stop of the rotator cuff is a key factor affecting the effect of surgery. In recent years, with the rapid development of tissue engineering, the repair of the tendon-bone interface of rotator cuff injuries has also made great progress. Different treatment methods have their own advantages, and the combined application of multiple strategies may be the most effective method.^[18]^

The biomimetic double-layer biofilm scaffold is prepared using natural small intestinal submucosa and chitosan, and Poly (lactic co glycolic acid) (PLGA) microspheres are used as controlled-release carriers of BMP-2, VEGF and PDGF. PLGA microspheres which could simulate the controlled release of BMP-2 in vivo and PLGA microspheres with sequential controlled release of VEGF and PDGF were combined into the inner and outer layers of the double-layer membrane scaffold respectively, and the bone marrow mesenchymal stem cells are inoculated in the periosteum The scaffold is used to construct a biomimetic periosteum with biological activity and loaded with stem cells, and then transplant it to the tendon-bone interface to promote tendon-bone healing. The biomimetic double-layer biofilm scaffold combines growth factors, repair scaffolds, and stem cells to reflect the combined application strategy. Therefore, this study will provide new ideas for the treatment of poor tendon bone healing after rotator cuff injury, and it is expected to reduce the incidence of rotator cuff nonunion and re-tear.

This study also has the following limitations: due to the influence of intervention methods, this study cannot be strictly double-blind, which may affect the results; lack of quantitative evaluation indicators for rotator cuff healing and secondary arthroscopic observation; the current protocol has a short follow-up time. If necessary, we will plan to extend the follow-up to observe the medium and long-term effects.
